## Abstract

**Background:**

There is a consensus that exercise therapy should be used as a therapeutic approach in chronic low back pain (CLBP) but little consensus has been reached about the preferential type of therapy. Due to the heterogeneity of the population no clear effect of specific therapy interventions are found. Probably a specific subgroup of the investigated population will benefit from the intervention and another subgroup will not benefit, looking at the total investigated population no significant effects can be found. Therefore there is a need for the development of clinical prediction rules (CPRs). Objectives for this trial are first, the derivation of CPRs to predict treatment response to three forms of exercise therapy for patients with nonspecific CLBP. Secondly, we aim to validate a CPR for the three forms of exercise therapy for patients with nonspecific CLBP.

**Methods/Design:**

The study design is a randomized controlled trial. Patients with nonspecific CLBP of more than three months duration are recruited at the Antwerp University Hospital (Belgium) and Apra Rehabilitation Hospital. After examination, patients are randomly assigned to one of three intervention groups: motor control therapy, general active exercise therapy and isometric training therapy. All patients will undergo 18 treatment sessions during nine weeks. Measurements will be taken at baseline, nine weeks, six months and at one year. The primary outcome used is the Modified Oswestry Disability Questionnaire score. For each type of exercise therapy a CPR will be derived and validated. For validation, the CPR will be applied to divide each treatment group into two subgroups (matched and unmatched therapy) using the baseline measurements. We predict a better therapeutic effect for matched therapy.

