### Study design

The development of a CPR consists of three consecutive phases. The first two are the derivation and validation phase.

In the derivation phase a CPR is derived from a number of variables that have predictive potential for therapy outcome. These variables are obtained from baseline measurements and have a multidimensional character (impairments, activities and/or participation and contextual factors). Data analysis is being used to calculate the most powerful combination of these variables to finally form the new derived CPR (see Figure 1 and ‘Data analysis’).

In the validation phase the derived CPR will be applied in a new study population. This application will result in matched patients (allocated in accordance with the CPR) and in unmatched patients (not in accordance with the CPR). The treatment success of both groups will be compared. The hypothesis is that treatment success will be higher in the matched group (Figure 2).

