### Randomization and blinding

In both phases patients will be randomly assigned to one of the three treatment groups after baseline testing. The responsible researcher will use a randomization list generated with Microsoft Excel® software (version 14.3.9, Microsoft Corporation, Zaventem, Belgium). Physiotherapists responsible for the treatment sessions are blinded for the results of baseline and follow-up measurements, which are being performed by the responsible researcher.In the validation phase a pre stratification will be used to ensure a 50:50 ratio between matched and unmatched therapy within one intervention group. Patients who have a strong preference for one of our intervention groups and therefore cannot be randomized will be asked to participate in a parallel cohort study. In this study similar baseline and follow-up measurements will be used.

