#### Validation phase

In the validation phase the intervention therapy stays the same, but new patients will be included. In this study design, the interest is that treatment success will be higher in the matched group than the unmatched group, which means a one-tailed hypothesis is used to calculate the power. In the validation phase we need 105 patients to detect a minimum clinically important difference (effect size 0.43) with 80% power using a one-tailed hypothesis. This means that three groups of 35 patients are needed to complete the whole trial. Again we assume a dropout rate of 54% into account and therefore aim to include 229 patients.

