#### Validation phase

In the validation phase new patients will be again assigned randomly into one of the three treatment groups. Based on the derived CPR determined in phase one, each intervention group will be divided into either ‘matched therapy’ or ‘unmatched therapy’. The recruitment, information form, informed consent, measurements, blinding and intervention procedure will be the same for both derivation and validation phase.

To verify intergroup differences at baseline, variables will be compared between groups using independent t tests, Mann-Whitney U tests, or chi-square tests of independence based on the nature of the data.

To examine the principle hypothesis (difference in treatment effect between matched and unmatched groups), a three-way repeated-measures analysis of variance will be performed with treatment group (motor control versus general active exercise therapy vs. isometric therapy) and classification subgroup (motor control versus general active exercise therapy versus isometric therapy) as between-subject variables and time (baseline, nine weeks, six months and one year) as the within-subject variable. The dependent variable is disability (MODI score). The hypothesis of interest is the three-way interaction, and the two-way interactions between time and treatment group and between time and classification subgroup. We hypothesize that outcome over time will not differ based on the randomized treatment group, or the classification subgroup, but will depend on the interaction between the treatment group and classification subgroup, such that patients randomized to matched treatment will have better outcomes than patients randomized to unmatched treatment. This hypothesis will be supported if the three-way interaction is significant, but the two-way interactions are not. Pairwise *post-hoc* comparisons will be performed at each follow-up period to further explore any significant interaction terms. In both the derivation and validation phase we will use an intention-to-treat analysis.

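### The validation phase is split, stratified and powered as a one-tailed matched-versus-unmatched comparison but decided by a multi-degree-of-freedom interaction, so the stated 80% power belongs to a different test.

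*Protocol article*

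**What the plan says.** All references are to the protocol article. Two structures for the validation comparison stand in it.

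**Matched versus unmatched.**
- Abstract, Methods/Design: "the CPR will be applied to divide each treatment group into two subgroups (matched and unmatched therapy) using the baseline measurements". The same paragraph promises: "For each type of exercise therapy a CPR will be derived and validated".
- Study design, of matched and unmatched patients: "The treatment success of both groups will be compared".
- Randomization and blinding: pre-stratification is to "ensure a 50:50 ratio between matched and unmatched therapy within one intervention group".
- Power analysis, Validation phase: "the interest is that treatment success will be higher in the matched group than the unmatched group". A one-tailed calculation with effect size 0.43 and 80% power gives 105 patients, 35 per therapy.
- Data analysis, Validation phase, first paragraph: "each intervention group will be divided into either ‘matched therapy’ or ‘unmatched therapy".

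**Interaction.** The third paragraph of that last section names the matched/unmatched difference as the main hypothesis. It then tests it by a repeated-measures analysis of variance with three therapies, three classes and four time points on the MODI score: "The hypothesis of interest is the three-way interaction, and the two-way interactions between time and treatment group and between time and classification subgroup". Support requires a significant three-way interaction together with non-significant two-way interactions. Pairwise post-hoc comparisons at each follow-up may explore significant terms; which pairs is not stated.

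**The concern.** The two structures answer different questions. Inside one arm, matched and unmatched patients receive the same therapy and differ only in baseline characteristics. That contrast asks whether rule-positive patients do better than rule-negative patients on this therapy. The interaction asks whether the benefit of a therapy depends on the kind of patient, which is what matching means.

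Two things are at stake. First, the sample size is justified for a directional comparison of two groups, while the deciding test is a multi-df F test, which has no one-tailed form. Readers cannot tell from the stated 80% what chance the trial has of meeting its own criterion.

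Second, a rule is to be validated for each therapy, but one omnibus interaction does not show which rule worked. The only per-therapy contrast spelled out is the split within an arm, which cannot separate prognosis from differential response. The derivation phase makes this a practical risk: each rule is built within its own arm with no predictor-by-therapy term described, and the predictors from the same earlier single-arm study are entered in every arm's model. General prognostic factors can therefore enter the rules, and the rules may overlap.

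**Working it through.** **Inputs.** From the power section: effect size 0.43, one-tailed, 80% power, 3 × 35 = 105 completers. From the randomisation section: 50:50 matched/unmatched within each arm. From the data analysis: three therapies by three classes. Assumed, because not given: alpha 0.05, SD 1, one follow-up change score in place of the four time points, and all prognostic effects.

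**1. The plan's own figure.** For two means, n per group = 2(1.645 + 0.842)²/0.43² = 66.9, so 67 per group and 134 in total, not 105. One-sided alpha 0.10 gives 98 in total. A baseline correlation of √(1 − 105/134) = 0.465 would give 105, but none is stated. The dropout step does reproduce: 105/0.46 = 228.3, so 229. The point below does not depend on this gap.

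**2. Power of the pooled matched/unmatched contrast at 105.** Φ(0.43 × √(52.5/2) − 1.645) = Φ(0.558) = 0.71.

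**3. Power of the deciding interaction.** Take exclusive classes and 108 patients for exact balance: 36 per arm, 18 matched and 9 in each other class. Every arm and every class is then half matched, so the main effects explain none of the matching effect. Noncentrality = 0.43² × 108 × 0.25 = 4.99. The noncentral F with 4 and 99 df at 0.05 gives power 0.38; simulation gave 0.376. The criterion also requires two non-significant two-way terms, so its full power can only be lower.

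**4. A prognosis-only class in the within-arm split.** Suppose one class does better by δ under every therapy and matching does nothing. In that class's own arm the expected matched/unmatched difference is δ.
- δ = 0.43, 17.5 per subgroup: Φ(0.43 × √8.75 − 1.645) = Φ(−0.373) = 0.35.
- δ = 0.8, 18 per subgroup: Φ(0.8 × √9 − 1.645) = Φ(0.755) = 0.77.

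These equal the power for a real matching effect of the same size.

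**5. The same prognosis in the pooled contrast.**
- Balanced exclusive classes: the good-prognosis class supplies 18 of 54 matched and 9 + 9 = 18 of 54 unmatched patients, so prognosis cancels. The simulated pass rate was 4% to 5%.
- Overlapping rules (three independent yes/no rules, each 50% positive and prognostic): matched patients are all positive on their arm's rule and unmatched patients all negative, so prognosis does not cancel. Simulated pass rates were 43%, 68% and 88% at 0.30, 0.43 and 0.60 SD. Adding the rule main effects to the model brought this back to 4% to 6%.

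**6. Prognosis under the plan's interaction.** With a common prognostic effect of 0.43 SD, the interaction was significant in about 5% of simulated trials and the full criterion was met in about 2%.

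**The case against.** The strongest reply is that the plan states only one test. Matched versus unmatched is the hypothesis, the interaction is its test, and the text ties the two together. No within-arm test is specified, so the splits could be read as labelling and stratification. The Study design section defines matched by allocation in accordance with the rule. A pooled contrast among patients randomised within exclusive classes would indeed be a randomised comparison. The exact form of post-hoc tests and per-rule estimates may also be left to an analysis plan.

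Much of this stands. A reader might infer that the plan would accept a merely prognostic rule as validated, or that its matched/unmatched comparison is non-randomised throughout. The document supports neither. The stated criterion would reject such a rule, partly because a time by class effect makes it fail. The high pooled pass rates arise only if patients can fit several rules or none, whereas the analysis names a single three-level class.

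The reply does not rescue the power statement, which is one-tailed and about two groups while the deciding test is neither. Nor does it supply a sound per-therapy contrast. The article also does not say how three rules become one class when a patient fits several or none, so the safe exclusive case is not secured.

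**Conclusion.** The concern holds as an inconsistency. The comparison that is described, stratified and powered is not the one that decides validation. On the assumptions above, the stated 80% corresponds to about 70% for the pooled one-sided contrast at 105 completers and about 38% for the 4-df interaction.

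Exposure to pure prognosis is confined to two situations. One is arm-by-arm validation, at about 35% to 77% for a class advantage of 0.43 to 0.8 SD. The other is a pooled unadjusted contrast with overlapping rules. The prognostic sizes are illustrations, since the protocol gives none. The four-time-point model was not simulated, so the interaction's power under that model may differ.

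**What to change.** Name one primary validation contrast and use it in the abstract, Study design, Power analysis and Data analysis: the matching effect from randomised therapy by rule or class status, in a model that contains the main effects of therapy and of rule or class. Define that status for patients who fit several rules or none. Report the effect pooled and for each rule, with confidence intervals. State that matched versus unmatched within one arm is descriptive and does not validate a rule. Restate the validation-phase power for this contrast without enlarging the sample.

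The cost is text and a less favourable power figure. As a one-sided 1-df test for 0.43 SD, the contrast has about Φ(√4.99 − 1.645) = 0.72 with balanced exclusive classes (108 patients). With three independent 50% rules, the variance of matched status left after the main effects is (1/4) × (2/3) = 1/6. Noncentrality is then 0.43² × 105/6 = 3.24, and power is about Φ(1.80 − 1.645) = 0.56. Per-rule estimates will be less precise than the pooled one. No new measurements or patients are needed, but the choice should be fixed before validation data are seen.

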**Discussion:**

A randomized controlled trial has not previously been performed for the development of a CPR for exercise therapy in CLBP patients. Only one CPR was described in a single-arm design for motor control therapy in sub-acute non-radicular LBP patients. In this study, a sufficiently large sample will be included in both the derivation and validation phase.

**Trial registration:**

This trial was registered with Clinicaltrials.gov on 10 February 2014, registration number: NCT02063503.

**Electronic supplementary material:**

The online version of this article (doi:10.1186/1745-6215-16-4) contains supplementary material, which is available to authorized users.

## Background

Low back pain (LBP) can be considered as an epidemic [1]. The European guidelines mention a lifetime prevalence of 84% [2]. About 5 to 10% of LBP patients develop chronic low back pain (CLBP), and 85% of these patients have nonspecific LBP [2]. Based on the European guidelines [2] nonspecific CLBP is defined as pain and discomfort localised below the costal margin and above the inferior gluteal folds, with or without referred leg pain, persisting for at least 12 weeks. Nonspecific LBP is not attributable to a known specific pathology such as infection, tumor, osteoporosis, fracture, structural deformity, inflammatory disorder (for example, ankylosing spondylitis), radicular syndrome or cauda equine syndrome.

The large group of patients meeting these criteria is heterogeneous and therefore these patients represent a treatment challenge for every clinician. There is a consensus that exercise therapy should be used as a therapeutic approach [2] but little consensus has been reached about the preferential type of therapy [3–14]. Due to the heterogeneity of the population no clear effect of specific therapy interventions are found. Probably a specific subgroup of the investigated population will benefit from the intervention and another subgroup will not benefit, looking at the total investigated population no significant effects can be found. In response to this, the European guidelines [2] express the need for the development of tools which improve the classification and identification of specific clinical sub-groups of nonspecific CLBP patients.

Haskins *et al*. [15] described 23 existing studies on clinical prediction rules (CPR) in LBP patients. Only two of those studies describe the development of CPR’s for active rehabilitation in LBP patients. One of those two discusses a McKenzie approach, which is not our point of interest since we are focusing on motor control therapy, general active exercises therapy and isometric training therapy.

The other study, Hicks *et al*. [16], developed two preliminary CPR’s in recurrent LBP patients: one for the success and one for the absence of success of motor control therapy. They performed a single-arm intervention study (no control group only motor control therapy) on 54 recurrent non-radicular LBP patients. After therapy, 39 patients were classified as ‘improved’ and 15 patients were classified as ‘not improved’. Multivariate regression analysis resulted in four positive prediction factors for motor control therapy. Presence of three or more of the predicting factors led to a positive likelihood ratio (LR+) of 4.0 (95% CI: 1.6 to 10.0) and increased the post-test probability of success with motor control therapy from 33 to 67%. Also, four negative predicting factors with motor control therapy were detected. The presence of two or more predicting factors led to a negative likelihood ratio (LR–) of 0.18 (95% CI: 0.08 to 0.38).

Brennan *et al*. [17] investigated the application of CPR’s in 123 acute and sub-acute nonspecific LBP patients based on the CPR by Hicks *et al*. [16] and Fritz *et al.*
[18]. The patients that were assigned to an intervention group that, according to the CPR, was not the best suitable therapy (unmatched) were considered as control patients. The patients that were assigned to an intervention group that, according to the CPR, was the best suitable therapy were considered as test patients (matched). They concluded larger improvements on the Modified Oswestry Disability Questionnaire (MODI) by the patients following the matched treatment, in comparison with those following the unmatched therapy, both at short and longer term (four and 52 weeks, respectively).

The implementation and validation of a CPR can lead to a decrease of health complaints and an increased quality of life for numerous patients. A higher number and a faster return to work, or less frequent absence of work over time, are expected. If the patient-customized therapy leads to a decrease of recurrence this can lead to a decrease in direct and indirect health costs.

Our research question is the development (derivation) and validation of a CPR for the choice of an exercise therapy type (motor control therapy, general active exercise therapy and isometric training therapy) in nonspecific CLBP patients. Based on the derived CPR, subgroups will be made, ultimately leading to detection of patients with a high chance for success with a certain type of exercise therapy. The CPR will be developed according to the correct methodological phases [19, 20].

## Methods/Design

Ethical approval (B300201215600) was obtained from the local ethics committees of the University of Antwerp, the Antwerp University Hospital and Apra Rehabilitation Hospital. The trial is registered at Clinicaltrials.gov, with the identification number: NCT02063503.

### Study design

The development of a CPR consists of three consecutive phases. The first two are the derivation and validation phase.

In the derivation phase a CPR is derived from a number of variables that have predictive potential for therapy outcome. These variables are obtained from baseline measurements and have a multidimensional character (impairments, activities and/or participation and contextual factors). Data analysis is being used to calculate the most powerful combination of these variables to finally form the new derived CPR (see Figure 1 and ‘Data analysis’).

In the validation phase the derived CPR will be applied in a new study population. This application will result in matched patients (allocated in accordance with the CPR) and in unmatched patients (not in accordance with the CPR). The treatment success of both groups will be compared. The hypothesis is that treatment success will be higher in the matched group (Figure 2).

**Figure 1 Fig1:**
[figure not shown]
**Flow chart representing the design of the derivation phase.**

**Figure 2 Fig2:**
[figure not shown]
**Flow chart representing the design of the validation phase.**

For both phases, a single blinded randomized controlled trial study design will be used. The project started in August 2014. Analysis of these data is planned for the end 2015.

### Patient recruitment

Patients will be recruited by doctors at the service of two settings located in Antwerp, the Antwerp University Hospital and the Apra Rehabilitation Hospital. Treatment and measurements will be performed at the site where the patient has been recruited.

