### Data analysis

#### Derivation phase

This phase aims to detect potential predictive variables for treatment success (dichotomous, yes or no) in a set of baseline measurements. A minimal decrease in the MODI score of six points is considered as treatment success [35].

Potential predictive variables are selected as follows: first, individual variables from the self-reports, history and physical examination are tested for their bivariate association with the reference standard using independent sample t tests, Mann-Whitney U tests or chi-square tests based on the nature of the data. Variables with a significance level of *P* <0.10 are retained as potential prediction variables. We chose a more liberal significance level at this stage to avoid excluding potential predictive variables.

Next, selected potential prediction variables and known predictors as determined in the study of Hicks *et al*. [16] are entered into a multiple linear regression equation to determine the optimal set of predictors. A significance of *P <*0.05 is used in this stage. Variables retained in the regression model are used to develop a multiple CPR for classifying patients as likely responders to treatment. This statistical analysis is performed for each treatment group (motor control therapy, general active exercise therapy and isometric training therapy).

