Third, we aim to include a sufficiently large sample, based on a power analysis. Hicks *et al*. [16] included 54 patients in their study but no power analysis is mentioned in their paper. If there are not enough patients included, the CPR is unlikely to be valid. We compared our calculated sample size with the sample size calculated in Brennan *et al*.’s [17] study design and found comparable results. In addition, we use an extra 54% inclusion target to compensate for the possible dropout rate [34]. We aim to recruit 489 patients in total (combined total for both phases of the study). We calculated that each year around 200 LBP patients start the back revalidation program in the Antwerp University Hospital. This is the same for the Apra Rehabilitation Hospital. Out of these 400 LBP patients around 50% have nonspecific complaints. This means that we need around 18 months to finish each phase. We will closely follow the inclusion procedure to make sure we meet our goals. The current study protocol describes only the derivation and validation phase, and not the impact phase. Future research should target this impact phase. The impact phase needs a completely different approach since it investigates the economic consequences of the implication of the CPR. It also depends on the outcome of the derivation and validation phase. Consequently, it is beyond the scope of the present paper.

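### Hospital is absent from the stated derivation and validation analyses and from the one named stratum, so a variable that only marks hospital could be selected as a predictor (minor; cheap to fix)

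*Protocol article*

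**What the plan says.** Under Patient recruitment, the protocol article states: "Patients will be recruited by doctors at the service of two settings located in Antwerp". It adds: "Treatment and measurements will be performed at the site where the patient has been recruited". The Discussion puts the yearly intake of low back pain patients at around 200 for the university hospital and says of the other: "This is the same for the Apra Rehabilitation Hospital". A roughly even split is therefore expected.

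Under Randomization and blinding: "The responsible researcher will use a randomization list generated with Microsoft Excel® software". One stratification is named, and only for the second phase: "In the validation phase a pre stratification will be used to ensure a 50:50 ratio between matched and unmatched therapy within one intervention group". Baseline and follow-up measurements are described in the words "which are being performed by the responsible researcher".

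The candidate predictors are listed under Baseline testing and in Table 3; hospital is not one of them. In the derivation analysis each variable is tested singly against treatment success: "Variables with a significance level of *P* <0.10 are retained as potential prediction variables". The retained variables and previously published predictors then enter a regression, separately in each arm. For validation, "a three-way repeated-measures analysis of variance will be performed with treatment group" and classification subgroup as between-subject factors and time as the within-subject factor. No hospital term appears in either analysis.

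**The concern.** The product of this trial is a prediction rule for each therapy. The rule is derived inside each arm by relating baseline findings to success. Random allocation makes the arms comparable with one another. It does nothing to separate, within an arm, the effect of a baseline finding from the effect of being treated at one hospital rather than the other.

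Suppose a finding is commoner at one hospital, and success is also commoner there for reasons unrelated to the finding. The finding will then look predictive. A rule built on it would partly identify the hospital and would not carry over to a third clinic.

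The article is not merely brief here. It spells out its stratum, its candidate list, its selection steps and its ANOVA factors, and hospital is in none of them.

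**Working it through.** The plan gives no figure for hospital, and no between-hospital difference is documented. All site effects below are therefore assumptions, shown over a range.

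**Inputs from the article.** Two hospitals, split about 50:50 (Discussion). Derivation: 120 completers in three arms of 40, 260 to be included, so 260/3 ≈ 87 per arm. Validation: 105 completers in three arms of 35, 229 to be included. Screening level P<0.10.

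**1. How the artefact arises.** Take a test unrelated to success within either hospital. Let test positivity and success both be 70% at one hospital and 30% at the other.
- Success in test-positives: 0.7×0.7 + 0.3×0.3 = 0.58.
- Success in test-negatives: 0.3×0.7 + 0.7×0.3 = 0.42.

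That is a spurious gap of 16 points. With 60% and 40% the values are 0.6×0.6 + 0.4×0.4 = 0.52 and 0.4×0.6 + 0.6×0.4 = 0.48, a gap of 4 points. The artefact needs hospital to be related to both the variable and success.

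**2. How often such a variable passes the screen.** Simulation, 20,000 runs per case: a continuous baseline variable with no within-hospital link to success, tested by the planned t test at P<0.10.

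| Assumed shift in variable; success by hospital | n=40, no hospital term | n=87, no hospital term | with hospital term |
|---|---|---|---|
| none; 50% vs 50% | about 10% | about 10% | about 10% |
| 0.5 SD; 40% vs 60% | 11.7% | 13.3% | about 10% |
| 0.8 SD; 40% vs 60% | 13.7% | 17.8% | about 10% |
| 0.8 SD; 35% vs 65% | 18.6% | 27.4% | about 10% |
| 1 SD; 35% vs 65% | 21.4% | 35.1% | about 10% |

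The excess grows with sample size because it is a bias, not noise.

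**3. Precision of the arm comparison.** With a 50:50 split and a between-hospital outcome difference of d within-hospital SDs, leaving hospital out multiplies the SD, and so the standard error, by √(1 + d²/4).
- d = 0.2: √1.01 = 1.005
- d = 0.3: √1.0225 = 1.011
- d = 0.5: √1.0625 = 1.031
- d = 0.8: √1.16 = 1.077

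For d of 0.2–0.5 the standard error rises by 0.5–3%, equivalent to 1–6% more patients (1 + d²/4).

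**4. Chance imbalance without a hospital stratum.** Exact hypergeometric calculation with three equal arms and hospitals split as evenly as possible. The range is the largest minus the smallest share from one hospital across the arms.

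| Arms | Mean range | Range of 20 points or more |
|---|---|---|
| 3×40 (completers) | 13.4 points | 22% of trials |
| 3×35 (completers) | 14.3 points | 27% |
| 3×86 (about 260 randomised) | 9.1 points | 2% |
| 3×76 (about 229 randomised) | 9.7 points | 3% |

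**5. The validation interaction.** 4,000 simulated trials of 105 patients, with subgroup membership driven strongly by hospital (60/20/20 vs 20/20/60) and a 0.8 SD hospital effect, equal in all arms, on a single change score. The treatment-by-subgroup test rejected in 5.6% of trials at a nominal 5%. The subgroup term rejected in 31%.

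**The case against.** The strongest reply is that this is a condensed article, and a site stratum or covariate is often left to the full protocol or analysis plan. For allocation in the derivation phase this has force: the article names no strata there at all, and one list shared by both hospitals is not stated. For the analyses it has less, because the candidate variables, selection steps and ANOVA factors are written out.

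The second reply is that the documented difference between hospitals is only where patients are treated and measured. A reader might infer that case mix, therapists and assessors differ too. The article does not say so. Eligibility criteria are common to both, measurements are attributed to the responsible researcher (possibly one person at both sites), and therapists are trained, follow a written protocol per arm and keep a session diary. The primary outcome is a questionnaire. This stands: the size of any hospital effect is unknown and could be small. These safeguards do not, however, address differences in the patients each hospital attracts.

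A reader might also infer that the validation result is biased because classification subgroup is not randomised. The planned test concerns the interaction of subgroup with treatment, and treatment is randomised. A hospital effect common to all arms leaves that test near its nominal level (step 5). It loads on the subgroup term instead. The article counts a significant time-by-subgroup interaction against its hypothesis, so an unmodelled hospital effect could obstruct support but would not manufacture it. False support would need the hospital effect to differ by therapy, for which the article gives no evidence.

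**Conclusion.** The point holds for the derivation phase and is minor. As written, the selection steps cannot distinguish a patient characteristic from a marker of hospital. If the hospitals differ in both that characteristic and success, the chance that a variable with no within-hospital value passes the screen rises from 10% to about 12–21% at 40 per arm and 13–35% at 87 per arm. The upper ends require large assumed differences (1 SD in the variable, 35% vs 65% success); the mildest case examined adds only 2–3 points.

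It would go too far to say that the arm comparison is biased. Randomisation keeps it unbiased on average. What remains is chance imbalance, with a mean range of 9–10 points at the planned randomised numbers and 13–14 points among completers, and a modest loss of precision. Large imbalances are common only if completers alone are counted; at about 260 and 229 randomised, with the stated intention-to-treat analysis, a range of 20 points or more occurs in 2–3% of trials.

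**What to change.** Include hospital as a fixed adjustment term in the derivation screen and in each per-arm regression. It serves to adjust the selection of predictors and should not become an item in the rule. Include hospital in the validation model as well. Since the effects of interest there are interactions with time, the term should be crossed with time.

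For patients still to be randomised, generate the allocation list in blocks separately for each hospital. In the validation phase, combine this with the existing matched/unmatched stratum.

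The cost is one degree of freedom per model (in the repeated-measures model, a further three within-subject degrees of freedom for four time points) and one extra list per phase. Hospital is known for every patient. Recruitment to the derivation phase has started, so stratification can cover only its remaining patients, but the analysis term is still available for everyone and the validation lists lie ahead.
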